# Evaluation of the Oxiris Membrane in Cardiogenic Shock Requiring Extracorporeal Membrane Oxygenation Support: Study Protocol for a Single Center, Single-Blind, Randomized Controlled Trial

**DOI:** 10.3389/fcvm.2021.738496

**Published:** 2021-10-11

**Keywords:** cardiogenic shock, heart failure, extracorporeal membrane oxygenation, artificial membrane, oxiris, endotoxin/blood, cytokines/blood, continuous renal replacement therapy

## Abstract

**Background:** Veno-arterial extracorporeal membrane oxygenation (VA-ECMO) is the rescue treatment proposed to patients with refractory cardiogenic shock. The VA-ECMO implantation promotes inflammation and ischemia-reperfusion injuries through the VA-ECMO flow, causing digestive mucosa barrier disrupture and inducing translocation of bacterial wall components—Lipopolysaccharides (LPS) with further inflammation and circulatory impairment. LPS is a well-studied surrogate indicator of bacterial translocation. Oxiris membrane is a promising and well-tolerated device that can specifically remove LPS. The main study aim is to compare the LPS elimination capacity of Oxiris membrane vs. a non-absorbant classical renal replacement (RRT) membrane in patients with cardiogenic shock requiring VA-ECMO.

**Methods:** ECMORIX is a randomized, prospective, single-center, single-blind, parallel-group, controlled study. It compares the treatment with Oxiris membrane vs. the standard continuous renal replacement therapy care in patients with cardiogenic shock support by peripheral VA-ECMO. Forty patients will be enrolled in both treatment groups. The primary endpoint is the value of LPS serum levels after 24 h of treatment. LPS serum levels will be monitored during the first 72 h of treatment, as clinical and cardiac ultrasound parameters, biological markers of inflammation and 30-day mortality.

**Discussion:** Oxiris membrane appears to be beneficial in controlling the VA-ECMO-induced ischemia-reperfusion inflammation by LPS removal. ECMORIX results will be of major importance in the management of severe cases requiring VA-ECMO and will bring pathophysiological insights about the LPS role in this context.

**Clinical Trial Registration:**
www.ClinicalTrials.gov, identifier: NCT04886180.

## Introduction

Cardiogenic shock is associated with high morbidity and mortality due to impaired tissue perfusion (1). Approximately, 10% of the patients with refractory shock to medical treatment require circulatory support (2). In this case, veno-arterial extracorporeal membrane oxygenation (VA-ECMO) is the bridge-to-recovery treatment of choice. Despite VA-ECMO support, patients with cardiogenic shock have high morbidity and mortality (≥50%) (3). Morbidity and mortality are due to several interconnected mechanisms: tissue hypoperfusion, ischemia-reperfusion phenomenon, and systemic inflammatory response following the cardiogenic shock and VA-ECMO implantation (4–7). These conditions are responsible for multiple organ failure (MOF) and death (1, 8).

The digestive tract mucosa barrier function is affected during the ischemia-reperfusion phase, being a catalyst for systemic inflammation and MOF progression (9, 10). Lipopolysaccharides (LPS) are bacterial wall components that can be found in the intestinal lumen. From animal model and human neonates' studies, it was demonstrated that ECMO-related SIRS may disrupt the intestinal mucosa (11–13), favoring LPS translocation into the plasmatic sector (8, 10, 14). Acute ischemic heart failure also induces intestinal hypoperfusion and intestinal mucosal injury thus LPS translocation (14). LPS translocation promotes systemic inflammation through the activation of toll-like receptors, then it worsens vasoplegia and MOF with further mucosal barrier disruptions entering a positive feedback loop (15). Systemic inflammation with LPS translocation and digestive barrier disruption plays a pivotal role in patient's evolution to MOF and death (12).

The Oxiris filter set has a 3-layer structure with a polyethyleneimine surface-treated and heparin-coated enhanced AN-69 membrane. This particular structure allows for several cytokines and LPS elimination (16). *In vitro* and human studies demonstrated that LPS adsorption decrease the cytokine, systemic inflammation, vasoplegia, with less harmful adverse effects on splanchnic perfusion (16, 17). Furthermore, Oxiris membrane may not be associated with more complications than the usual continuous venovenous hemofiltration membrane (17). The ability of the Oxiris membrane to eliminate cytokine and bind LPS suggests that it might be a potential candidate to control the magnitude of the ischemia-reperfusion-induced inflammation, in order to impair the bacterial translocation and progression to MOF. To our knowledge, there is no published or ongoing clinical trial evaluating the Oxiris membrane in patients with cardiogenic shock support by VA-ECMO.

Our hypothesis is that the early treatment by the Oxiris membrane in patients with cardiogenic shock support by VA-ECMO would allow the removal of LPS and pro-inflammatory cytokines, thus controlling systemic inflammation, vasoplegia, MOF, and death.

## Materials and Methods

### Study Design

ECMORIX is a randomized, prospective, single-center, single-blind, parallel-group, controlled study. It compares the Oxiris membrane vs. the standard RRT care in patients with cardiogenic shock support by VA-ECMO. The study was approved by an independent ethics committee (Ethics Committee No. 2-21-005 id11120, French CPP Sud-Ouest et Outre-Mer 2) and was registered on Clinicaltrials.gov (NCT04886180). The study is conducted at the cardio-vascular ICU of the university-affiliated tertiary hospital of Dijon, France. All patients or their next of kin received written information about the study and gave their written consent to participate. The study design adheres to the requirements of the Medical Research Involving Human Subjects Act and of the Declaration of Helsinki.

The Standard Protocol Items: the study follows the SPIRIT Recommendations for Interventional Trials, and the SPIRIT protocol chronology is presented in Table 1. The first patient was included in May 2021, and the last patient follow-up is planned for June 2024.

**Table 1 T1:** Protocol chronology of the study.

	**ICU admission/ECMO implantation**	**Enrollment**	**Follow-up**					**End of study**
	**H-12 (Day 0)**	**H0 (Day 0)**	**H6**	**24H (Day 1)**	**48H (Day 2)**	**72H (Day 3)**	**Day 7**	**Day 30**
Enrollment validation	X							
Randomization and membrane placement		X						
Clinical examination	X							
Standard analysis set	X	X	X	X	X	X		
Study analysis set	X	X	X	X	X	X		
Clinical and biological data collection		X	X	X	X	X	X	X
Echocardiography		X	X	X	X	X	X	X

*ICU, intensive care unit; ECMO, extracorporeal membrane oxygenation; H, hours before or after enrollment*.

### Study Population

Adult patients are considered for enrolment if they have cardiogenic shock support by VA-ECMO, with an indication for renal replacement therapy (RRT). The inclusion, non-inclusion and exclusion criteria are provided in Table 2.

**Table 2 T2:** Inclusion, non-inclusion and exclusion criteria of the study.

**Inclusion criteria**	**Non-inclusion criteria**
• Age ≥18 years	• Age <18 years
• Family or legal responsible agreement	• Pregnant or breastfeeding patient
• Refractory cardiogenic shock treated with ECMO and requiring RRT	• Severe bleeding under ECMO • No medical insurance
• Inclusion in ≤ 12 h since ECMO implantation	• Patient under court order
	• Patient under legal protection
	**Exclusion criteria**
	• ≤ 24 h of duration of Oxiris or RRT treatment

*ECMO, Extracorporeal membrane oxygenation; RRT, renal replacement therapy; h, hours*.

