### Study Intervention

All patients are treated with peripheral venous-arterial femoro-femoral ECMO. Care for patients supported by VA-ECMO is standardized, as previously described (18, 19), and follow patients care practice ESLO guidelines^1^.

Enteral nutrition is started within 24 h of ECMO starting after obtaining hemodynamic stabilization. The enteral nutrition rate follows international guidelines (20). The feeding dose and flow rate is progressively increase on several days (20).

The study treatment consists of either continuous RRT using the Oxiris membrane or an ST150 PrismaFlex membrane for 72 h, respecting the randomization. The continuous RRT is initiated and managed according to the usual practice, only the type of RRT filter membrane is different. The RRT is standardized to continuous veno-venous hemofiltration (CVVH), with a patient dose of 30 ml/kg/h, a predilution of 1/3, and a postdilution of 2/3. The blood flow rate is set between 150 and 350 ml/min to obtain a filtration fraction ratio of 20%. Ultrafiltration rate is set according to patient volemia status. For both groups, the RRT system is incorporated to the VA-ECMO system, as part of routinely process in our ICU.

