### Randomization

The 1:1 ratio randomization is performed by the investigator after the patient's enrollment, using a dedicated e-platform made with CleanWeb TM. This process is controlled by individual usernames and newly created passwords for each enrollment. A second checkup for the inclusion, non-inclusion and exclusion criteria is done at this point. Technical support is provided by the Research Methodology Support Unit from our university-affiliated hospital, which also keeps a record of the full randomization process.

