### Endpoints or Outcome Measures

The primary endpoint is the LPS serum level after 24 h of continuous RRT with Oxiris membrane.

The secondary endpoints are: (1) the VIS score [defined using the formula: Dopamine infusion rate (mcg/kg/min) + Dobutamine infusion rate (mcg/kg/min) + 100 x Epinephrine infusion rate (mcg/kg/min) + 10 x Milrinone infusion rate (mcg/kg/min) + 10,000 x Vasopressin infusion rate (units/kg/min) + 100 x Norepinephrine infusion rate (mcg/kg/min)]; (2) the SOFA score at day 1, 2, 3 and 7; (3) Serum levels kinetic of cytokines (IL1, IL6, IL 4, IL10, TNF-alpha, interferon gamma, MCP1), CRP, procalcitonin, I-FABP, GLP-1, zonuline, citrulline from RRT initiation, to 6 h after initiation, day 1, day 2, and day 3 of treatment; (4) LPS plasma concentration, (5), ICU length of stay and 30-day mortality. Patients' follow-up is 30 days after initiation of VA-ECMO.

Serial standard usual blood analysis set is drawn at several time points: at the enrollment moment (before RRT membrane placement), after 6, 24, 48, and 72 h of continuous RRT. The study-specific blood analyses are performed at the same time moments. The reference time (T0) is the start of RRT for all group (control and intervention).

At each time point, one EDTA tube of 5 ml is taken via the arterial catheter, and 2 sets of EDTA tubes of 5 ml and are taken on the RRT circuit (one before and one after the filter membrane).

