### Statistics

#### Sample Size Calculation

Based on a LPS mean value of 110 ± 40 pmol/l (21), 34 patients should be randomized, 17 in each treatment arm will be necessary to demonstrate a decrease over 35% (16), with a bilateral alpha risk of 5% and a power of 80%. Assuming that 15% of patients would not be evaluable due to early death, we fixed the sample size to 40 patients, 20 patients in each treatment arm.

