#### Data-Analysis Plan

The data will be analyzed in intention-to-treat and per-protocol. The variables will be presented as mean ± SD, or as median [25–75% IQR], as appropriate. The treatment groups will be presented comparatively after the randomization. The qualitative variables will be compared using the Chi-square test or Fisher's exact test. The quantitative variables will be compared using the Student's test or a non-parametric test, as appropriate. Longitudinal data will be processed using mixed-models. The normality will be checked graphically, with histograms and QQ plots and using the Shapiro-Wilk normality test.

The evaluation of the primary endpoint will be considered as a comparison of means. The statistical analysis will be performed using R Studio software. A *p* < 0.05 will be considered statistically significant.

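### The only exclusion criterion, 24 h or less of treatment, can be known only after randomisation and, applied as written, conflicts with the planned intention-to-treat analysis

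*Protocol article*

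**What the plan says.** Table 2 separates non-inclusion criteria, which can all be judged before enrolment, from a single exclusion criterion: "≤ 24 h of duration of Oxiris or RRT treatment". Table 1 places "Randomization and membrane placement" in the H0 column. Study Intervention plans treatment for 72 h in either arm ("ST150 PrismaFlex membrane for 72 h, respecting the randomization").

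Three other statements bear on the criterion:

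- Randomization: "A second checkup for the inclusion, non-inclusion and exclusion criteria is done at this point".
- Data-Analysis Plan: "The data will be analyzed in intention-to-treat and per-protocol". The section does not link the 24 h rule to either set.
- Sample Size Calculation: "Assuming that 15% of patients would not be evaluable due to early death", which takes the total from 34 to 40.

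The primary endpoint is worded as "The primary endpoint is the LPS serum level after 24 h of continuous RRT with Oxiris membrane". The secondary endpoints include "ICU length of stay and 30-day mortality".

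**The concern.** How long a patient was treated is an event after randomisation. A patient can fall short of 24 h by dying early, which the sample size section expects, and the trial's hypothesis in the Introduction is that the membrane affects organ failure and death. The selection event may therefore depend on the allocated arm.

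A trial-level exclusion on that event cannot coexist with an analysis of all randomised patients. Whoever writes the analysis must either follow Table 2 and lose intention-to-treat, or follow the Data-Analysis Plan and ignore Table 2. At stake are the randomised basis of the LPS comparison and the completeness of the 30-day mortality count, in a population for which the Introduction quotes mortality of at least 50%.

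**Working it through.** **1. Timing.** Randomisation and membrane placement are both at H0, and the Endpoints section sets T0 at the start of RRT in both groups. Duration of treatment at or below 24 h can be established only between H0 and H24. A pre-randomisation reading fails: Oxiris is itself the allocated treatment, and inclusion is within 12 h of ECMO implantation. The check of exclusion criteria at randomisation therefore cannot cover the only exclusion criterion listed.

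**2. The plan's sample size.** Inputs: mean 110, SD 40, decrease 35%, two-sided alpha 5%, power 80%.

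- Difference: 0.35 × 110 = 38.5 pmol/l.
- n per arm = 2 × [40 × (1.960 + 0.842) / 38.5]² = 16.94, so 17 per arm and 34 in total.
- 34 / 0.85 = 40.

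The stated figures reproduce. The plan expects 0.15 × 40 = 6 randomised patients not to be evaluable.

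**3. 30-day mortality.** That deaths within 24 h leave the comparison follows from the rule as written; the effect on the result depends on how they fall. Assume 10 deaths among 20 in each arm, 6 of the 20 deaths being early:

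| Early deaths, Oxiris / ST150 | Mortality after exclusion | All randomised |
|---|---|---|
| 3 / 3 | 7/17 = 41% vs 7/17 = 41% | 50% vs 50% |
| 1 / 5 | 9/19 = 47% vs 5/15 = 33% | 50% vs 50% |

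An even split understates mortality equally in both arms and leaves the contrast intact. The 1/5 split creates a false 14-point difference. If early death is unrelated to arm, a split of 1/5 or more uneven, in either direction, has hypergeometric probability 2 × (0.081 + 0.010) = 18%. The 1/5 split is a constructed example, not a forecast.

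**4. 24 h LPS.** Assume no treatment effect, LPS normal with mean 110 and SD 40, a severity score correlated 0.5 with LPS, and loss of the sickest fraction q. The mean of those retained falls by 0.5 × 40 × φ(z) / (1 − q), where z is the (1 − q) normal quantile.

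- q = 5%: 20 × 0.1031 / 0.95 = 2.2.
- q = 15%: 20 × 0.2332 / 0.85 = 5.5.
- q = 25%: 20 × 0.3178 / 0.75 = 8.5.
- q = 30%: 20 × 0.3477 / 0.70 = 9.9.

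| Losses by arm | Spurious difference (pmol/l) | Simulated type I error |
|---|---|---|
| 15% / 15% | 0 | about 5% |
| 5% / 25% | 6.3 | about 7% |
| 0% / 30% | 9.9 | about 10–11% |

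Type I errors come from t-tests on simulated trials with 20 randomised per arm. The simulated difference for 5%/25% was 6.5 with 8,000 trials and 6.3 with 60,000. Against the planned 38.5, 6.3 is 16%.

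**5. Power if early stoppers are kept.** Assume a fraction of patients stop early, survive and show none of the effect, with 20 per arm and SD 40 unchanged. Power = Φ[difference / (40 × √(2/20)) − 1.960], where 40 × √(2/20) = 12.65.

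- 0%: Φ(38.5/12.65 − 1.960) = 86%.
- 15%: difference 0.85 × 38.5 = 32.7; Φ(2.587 − 1.960) = 73% (71% by the t distribution).

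For reference, 17 per arm with no dilution gives 80% (78% by the t distribution).

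**The case against.** The strongest reply is that Table 2 does not say what the patient is excluded from. The sponsor may have meant the rule only for the per-protocol set; that reading keeps the two planned analyses distinct, and nothing in the objectives or endpoints says that 30-day mortality omits early deaths. This stands as a limit. A reader might infer that every comparison in the trial is conditioned on surviving and being treated beyond 24 h. That holds only if the rule governs all analyses, which the article does not state. It does not remove the conflict: the rule is listed as a study exclusion criterion without restriction, and the text must say where it applies.

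Other strong inferences are not supported:

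- **LPS bias as a certainty.** It needs losses that differ by arm, and the article gives no sign that they will. Assuming that exactly the highest LPS values are lost would be a worst case.
- **Filter clotting as a trigger.** The rule concerns duration of treatment. A replaced filter may not end treatment, and early death is the only reason for non-evaluability that the article names.
- **A power loss from 25% being removed.** No such rate appears in the article.
- **Failure to name a primary analysis set.** That can be left to a full protocol or SAP that is not shown.

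Dropping the rule also does not recover an LPS value for a patient dead before 24 h. A mixed model would not solve this, since it would implicitly estimate LPS after death. Replacing the stated comparison of means would be a preference, not a correction.

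**Conclusion.** The point holds as an internal contradiction. The only exclusion criterion is a post-randomisation event, cannot be applied at the stated check, and, if followed as written, prevents an intention-to-treat analysis and removes deaths within 24 h of treatment from the 30-day mortality comparison. These conclusions rest on the text alone.

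The number affected, about 6 of 40, is the plan's own allowance for early death; the rule itself is not limited to death. The size of any LPS bias is hypothetical: zero with equal losses, and about 6 to 10 pmol/l under the unequal losses assumed above. The sample size arithmetic is not in question. The contradiction should be resolved before analysis, because in a trial of 40 a few patients moved in or out of the analysis can change the result.

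**What to change.** 1. Delete the 24 h rule from the exclusion criteria in Table 2 and use it only to define the per-protocol set. The check at randomisation then covers only criteria knowable at that time.
2. State in the Data-Analysis Plan that the intention-to-treat set is all randomised patients, analysed as randomised.
3. Analyse 30-day mortality in all 40 randomised patients.
4. Take the H24 LPS sample, already scheduled in Table 1, in every living patient even if the study treatment has stopped, and word the primary endpoint as LPS 24 h after T0 in both arms.
5. Keep the stated comparison of means as the primary analysis. Patients who die before 24 h have no LPS value; cover them in a prespecified sensitivity analysis, for example one assigning them the worst rank.

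The cost is a wording change and an assurance that the scheduled sample is taken in the few patients who stop early. The real downside is dilution of the LPS effect by early stoppers: power falls below 80%, to about 73%, if 15% stop early, survive and show no effect. That rate is an assumption; the sponsor should state the rate it expects and confirm that 40 patients remain enough.

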### Study Intervention

All patients are treated with peripheral venous-arterial femoro-femoral ECMO. Care for patients supported by VA-ECMO is standardized, as previously described (18, 19), and follow patients care practice ESLO guidelines^1^.

Enteral nutrition is started within 24 h of ECMO starting after obtaining hemodynamic stabilization. The enteral nutrition rate follows international guidelines (20). The feeding dose and flow rate is progressively increase on several days (20).

The study treatment consists of either continuous RRT using the Oxiris membrane or an ST150 PrismaFlex membrane for 72 h, respecting the randomization. The continuous RRT is initiated and managed according to the usual practice, only the type of RRT filter membrane is different. The RRT is standardized to continuous veno-venous hemofiltration (CVVH), with a patient dose of 30 ml/kg/h, a predilution of 1/3, and a postdilution of 2/3. The blood flow rate is set between 150 and 350 ml/min to obtain a filtration fraction ratio of 20%. Ultrafiltration rate is set according to patient volemia status. For both groups, the RRT system is incorporated to the VA-ECMO system, as part of routinely process in our ICU.

### Randomization

The 1:1 ratio randomization is performed by the investigator after the patient's enrollment, using a dedicated e-platform made with CleanWeb TM. This process is controlled by individual usernames and newly created passwords for each enrollment. A second checkup for the inclusion, non-inclusion and exclusion criteria is done at this point. Technical support is provided by the Research Methodology Support Unit from our university-affiliated hospital, which also keeps a record of the full randomization process.

### Objectives

The primary objective is to compare the LPS concentration at 24 h between Oxiris membrane vs. a non-absorbent classical membrane (ST150) in patients with cardiogenic shock support by VA-ECMO.

The secondary objectives are (1) to evaluate the effect of Oxiris membrane treatment on the severity of vasoplegic circulatory failure assessed by the vasoactive-inotropic score (VIS); (2) to evaluate the effect of Oxiris membrane treatment on organ failure using the Sequential organ failure assessment (SOFA) score; (3) to evaluate the effect of Oxiris membrane treatment on inflammation and digestive tract barrier disruptor; (4) to describe the Oxiris membrane LPS elimination kinetic profile; (5) to evaluate the Oxiris membrane treatment on the intensive care unit (ICU) length of stay and 30-day mortality.

### Endpoints or Outcome Measures

The primary endpoint is the LPS serum level after 24 h of continuous RRT with Oxiris membrane.

The secondary endpoints are: (1) the VIS score [defined using the formula: Dopamine infusion rate (mcg/kg/min) + Dobutamine infusion rate (mcg/kg/min) + 100 x Epinephrine infusion rate (mcg/kg/min) + 10 x Milrinone infusion rate (mcg/kg/min) + 10,000 x Vasopressin infusion rate (units/kg/min) + 100 x Norepinephrine infusion rate (mcg/kg/min)]; (2) the SOFA score at day 1, 2, 3 and 7; (3) Serum levels kinetic of cytokines (IL1, IL6, IL 4, IL10, TNF-alpha, interferon gamma, MCP1), CRP, procalcitonin, I-FABP, GLP-1, zonuline, citrulline from RRT initiation, to 6 h after initiation, day 1, day 2, and day 3 of treatment; (4) LPS plasma concentration, (5), ICU length of stay and 30-day mortality. Patients' follow-up is 30 days after initiation of VA-ECMO.

Serial standard usual blood analysis set is drawn at several time points: at the enrollment moment (before RRT membrane placement), after 6, 24, 48, and 72 h of continuous RRT. The study-specific blood analyses are performed at the same time moments. The reference time (T0) is the start of RRT for all group (control and intervention).

At each time point, one EDTA tube of 5 ml is taken via the arterial catheter, and 2 sets of EDTA tubes of 5 ml and are taken on the RRT circuit (one before and one after the filter membrane).

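### ICU length of stay is compared between arms with no account of death, so if Oxiris saves lives the crude comparison can point the wrong way

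*Protocol article*

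**What the plan says.** Under Endpoints or Outcome Measures, secondary endpoint 5 is "ICU length of stay and 30-day mortality". The Objectives section presents the same pair as a treatment effect to be evaluated, so stay is a between-group outcome. The same section fixes the horizon: "Patients' follow-up is 30 days after initiation of VA-ECMO". Secondary endpoint 2 is "the SOFA score at day 1, 2, 3 and 7".

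The Data-Analysis Plan gives general rules by type of variable. For stay the applicable one is: "The quantitative variables will be compared using the Student's test or a non-parametric test, as appropriate". For serial SOFA it is: "Longitudinal data will be processed using mixed-models".

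The Introduction says that "patients with cardiogenic shock have high morbidity and mortality (≥50" (a percentage; no time horizon is given). In the statistics sections death appears once, under Sample Size Calculation, as the reason for enlarging the sample: "Assuming that 15% of patients would not be evaluable due to early death". The article does not restrict stay to survivors, treat death as a competing event, or give SOFA a value after death.

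**The concern.** Stay in the ICU ends in one of two opposite ways: discharge alive or death. Crude stay treats both as the same event and reads shorter as better. A patient who dies on day 2 then scores better than one who leaves alive on day 20. Moving from a Student's test to a rank test does not help, because the early death still gets the more favourable rank.

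This matters because the Introduction's hypothesis is that Oxiris controls organ failure and death. If that is true, the Oxiris arm contains more survivors, who are the likely long stayers, and secondary objective 5 may show an apparent harm produced by the benefit itself.

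SOFA has a related but weaker problem. Scores stop at death, and a mixed model fitted to the observed scores implicitly carries each trajectory on past death, where no score exists.

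**Working it through.** **The plan's own figure.** The article gives no figure for ICU stay or SOFA. Its one sample-size figure concerns LPS. With a mean of 110, SD 40 and a 35% decrease (38.5 pmol/l), n per arm = 2 × (1.960 + 0.842)² × 40² / 38.5² = 16.9, so 17, or 34 in total. Then 34 / 0.85 = 40. This reproduces the article, and the point below does not touch it.

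**Direction of the bias in stay.** Let m be mortality, D the mean stay of patients who die and S the mean stay of survivors, with D and S the same in both arms.

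- Crude mean stay = m·D + (1 − m)·S.
- Difference, Oxiris minus control = (m_control − m_Oxiris) × (S − D).

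The difference is positive (Oxiris looks worse) whenever Oxiris mortality is lower and S exceeds D. It is zero when mortality is equal.

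**Illustration.** Control mortality of 50% is the lower bound of the Introduction's figure. Oxiris mortality of 35%, D = 6 days and S = 18 days are assumptions.

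- Control: 0.50 × 6 + 0.50 × 18 = 12.0 days.
- Oxiris: 0.35 × 6 + 0.65 × 18 = 13.8 days.
- Difference: 0.15 × 12 = 1.8 days longer with the better survival.

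**Range.** A simulation used 20 patients per arm, 5,000 runs, a Mann-Whitney test, and lognormal stays identical in both arms given vital status (log SD 0.7 in deaths, 0.5 in survivors, no cut at day 30). The three pairs of assumed median stays (deaths / survivors) were 4 / 15, 7 / 20 and 10 / 15 days.

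| Mortality, control vs Oxiris | Excess mean stay, Oxiris | Trials with longer mean stay in Oxiris | Significantly longer |
|---|---|---|---|
| 50% vs 50% | about 0 d | 49–51% | 2–3% |
| 50% vs 40% | 0.5 to 1.3 d | 56–67% | 4–7% |
| 50% vs 30% | 0.8 to 2.7 d | 62–79% | 5–15% |

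About 2.5% in the last column is expected by chance.

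**ICU-free days to day 30, death = 0.** The mean is (1 − m) × E[max(0, 30 − stay)] among survivors. If survivors' stays are the same in both arms, the arm with fewer deaths always has the higher mean.

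- If every survivor stays exactly 18 days, or at least leaves by day 30: 0.50 × 12 = 6.0 vs 0.65 × 12 = 7.8.
- If survivors' stays are exponential with mean 18: 30 − 18 × (1 − e^(−30/18)) = 15.4, giving 7.7 vs 10.0.

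The figures depend on the assumed distribution; the order does not. In the simulation with 50% vs 30% mortality, the means were 6.9 vs 9.6, 4.8 vs 6.8 and 6.8 vs 9.6 for the three stay pairs.

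**SOFA among survivors only.** Assume scores of 12 ± 4 (normal), the highest scorers die, and 30% vs 15% are dead by day 7. Survivor means are then 10.0 vs 10.9, so the arm with fewer deaths looks worse with no true difference. This tests a comparison restricted to survivors, not the planned mixed model. It shows why the model should not be restricted to survivors.

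**The case against.** The strongest reply is that this is a condensed article. Its analysis paragraph is generic, names neither stay nor SOFA, and an unseen analysis plan may hold a rule for deaths. That lowers the weight of the point but does not remove it. The article makes stay a between-group outcome and assigns quantitative variables a test. Followed as written, that test favours early death, and any further rule would have to override it.

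A second reply is that mortality stands beside stay in the same endpoint, so a reader would see fewer deaths next to longer stays. That is fair, and it limits the damage. It does not correct the stay comparison, and at 20 per arm the mortality result would be weak. For 50% vs 35%, z = 0.15 / √(0.425 × 0.575 × 2/20) = 0.96. The likely report is a non-significant mortality difference next to a longer stay.

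Third, the size rests on assumption. The article gives no stays, no times of death and no expected mortality effect, and its 50% has no time horizon. This stands in full.

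A reader might also infer that the planned SOFA analysis is biased against Oxiris because sicker patients stay in the comparison. The article does not support that. A likelihood-based mixed model uses the earlier, often high, scores of patients who later die, so it is not a comparison of survivors' raw means. Its weakness is extrapolation past death. Nor does the article say that stays are cut off at day 30; it gives only a 30-day follow-up.

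**Conclusion.** The point holds for ICU length of stay. As written, the comparison takes no account of death in a population where at least half are expected to die, and it points the wrong way if Oxiris lowers mortality and deaths have shorter stays than survivors. Only the direction follows from that reasoning. The size does not: 1.8 days in the illustration, and 0.5 to 2.7 days across the assumed scenarios with a mortality difference of 10 to 20 points. With equal mortality the bias is about zero. It would be too strong to say that the stay result will mislead. Even with a 20-point mortality benefit, only 5–15% of simulated trials showed a significantly longer stay.

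For SOFA the conclusion is narrower: the mixed model needs a sensitivity analysis that gives death a defined place. These are secondary endpoints with mortality reported alongside, so this is a modest correction.

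**What to change.** 1. Replace crude ICU length of stay with ICU-free days to day 30, scoring 0 for any patient dead by day 30, and compare the arms by a rank test. Count from the start of VA-ECMO, the origin already used for follow-up. Alternatively, analyse time to ICU discharge alive with death as a competing event.
2. Keep 30-day mortality as a separate outcome. Crude stay can still be described by vital status, without a test.
3. Keep the mixed model for SOFA in all randomised patients. Add a sensitivity analysis that ranks death as the worst outcome at each of days 1, 2, 3 and 7. Do not restrict the mixed model to survivors, because survival is itself a post-randomisation outcome.

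The cost is wording in the analysis plan. Stay, 30-day mortality and SOFA are already endpoints, so no patients or visits are added; the competing-event option also needs the date of death, which should be confirmed as an eCRF item. The small downside is that ICU-free days mix survival with stay and are less intuitive than days in the ICU, which is why mortality must still be shown on its own. The LPS endpoint and the sample size of 40 stay as they are.
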